### Statistical Analysis

#### Overview

Analyses will be conducted after data collection. As this is a feasibility study, the primary analytic aims are to describe data availability, engagement, and retention, and to explore preliminary associations between wearable-derived features and mental health outcomes. All analyses will be exploratory and will inform the design of a future larger study.

#### Descriptive and Feasibility Analyses

Baseline characteristics will be summarized using standard descriptive statistics. Questionnaire outcomes will be described at T0, T1, T2, and T3. Feasibility outcomes (recruitment rate, retention, questionnaire completion, proportion of valid wear days and weeks, and completeness of each wearable stream) will be reported using counts, percentages, medians, and IQRs as appropriate. Participants will be grouped into quartiles of data completeness to assess engagement patterns as undertaken in prior work [40,41].

#### Wearable Feature Construction

Wearable data (steps, active minutes, sleep metrics, heart rate, HRV, stress, and body battery) will be summarized at the day and week level. Features will include mean values, variability measures, and simple temporal trends. Final feature inclusion for ML analysis will depend on data completeness. All sensor-derived features will be treated as exploratory physiological indices and not as validated clinical biomarkers.

#### Missing Data

For wearable data, a valid day will be defined as having at least 6 hours of data for each individual stream. Weekly summaries will require at least 4 valid days. Missing days and weeks will not be imputed in the primary analysis. Patterns of missingness will be summarized and reported.

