This study aims to explore the associations between CMDs, including symptoms of anxiety and depression measured monthly using the 12-item General Health Questionnaire (GHQ-12), and indicators of physical activity recorded by wrist-worn fitness trackers among UK veterans. Garmin-derived metrics include steps, active minutes per day, HRV, stress levels, and overall activity patterns. In addition, the study seeks to examine the relationship between mental health and broader functioning factors, such as somatic symptoms, loneliness, and sleep, in relation to physical activation metrics (steps, active minutes per day, HRV, stress, and activity) obtained from fitness trackers. The primary outcome of interest is the change in GHQ-12 score from baseline (T0) to day 84 (T3) associated with the change in physical activity over the 3-month study period. The study also aims to assess the feasibility of using fitness trackers to enhance the prediction and management of CMDs among UK veteran populations, to inform the development of a potentially larger-scale initiative. Feasibility will be assessed through recruitment rate, retention rate, and data completeness of both watch-derived data and monthly questionnaire responses. By integrating objective physiological data with self-reported mental health measures, this work ultimately aims to support improved monitoring and intervention strategies for CMDs within the veteran population.

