### Wearable Tracker

Garmin devices (Figure 2) are consumer-grade wearables widely used in health research. Existing validation studies have demonstrated acceptable accuracy for step counting, heart rate, HRV-derived indices, and sleep duration in free-living and laboratory conditions. While these metrics do not replace clinical gold standards, they are considered reasonable proxies for exploratory digital phenotyping studies and have been used in hundreds of published research projects [34]. The device is therefore suitable for feasibility work focusing on patterns of association rather than clinical diagnosis. For this study, the Garmin vívosmart-5 will be used. This device is Conformité Européenne marked and approved for sale and use in the United Kingdom. The device has a battery charge of 7 days and can store data for up to 2 months.

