### Sensor Modalities

Sensors included a Garmin Elevate wrist heart rate monitor, Pulse Ox blood oxygen saturation monitor, accelerometer, ambient light sensor (for display brightness adjustment), device-generated values (sleep, stress, maximal oxygen consumption, and zero-crossing), and human-recorded events (activities and body composition; Table 3).

**Table 3 table3:** Garmin vívosmart-5 sensor modalities.

Data type	Variables/description	Sensor
Energy (body battery)	Composite energy score derived from physiological signals	Garmin device (algorithm-generated)
Heart rate	Resting heart rate; heart rate (beats per minute); beat-to-beat interval; heart rate variability	Garmin Elevate wrist heart rate monitor
Respiration	Respiratory rate summaries	Pulse oximeter
Sleep	Sleep score, sleep duration (hours), and sleep quality	Garmin device (algorithm-generated)
SpO_2_^a^	Blood oxygen saturation level	Pulse oximeter
Stress	Physiological stress score derived from heart rate variability	Garmin device (algorithm-generated)
Physical activity	Step count, active minutes, and self-reported activity	Accelerometer; actigraphy; self-reported (human-recorded events)

^a^SpO_2_: saturation peripheral oxygen.

Each smartwatch package includes the following items: Garmin vívosmart-5, USB-C charging cable, and user manual. Participants will be provided with the complete set, consisting of the device and all accompanying contents listed. Participants will be sent instructions on the proper handling and operation of the device. If requested, participants can arrange a video call with a member of the research team to support setup. The manufacturer of the watch, Garmin, will not have access to any study data. At the end of the study, participants can opt to retain the device or send it back to the research team via a prepaid postage box.

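### The valid-day rule counts hours of data rather than hours of wear, so unworn days can pass as valid activity days if off-wrist time is logged as zero steps

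*Protocol article*

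**What the plan says.** The Missing Data section fixes validity in three sentences. At day level, "a valid day will be defined as having at least 6 hours of data for each individual stream". At week level, "Weekly summaries will require at least 4 valid days". On gaps, "Missing days and weeks will not be imputed in the primary analysis". None of them mentions whether the watch was on the wrist.

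The Descriptive and Feasibility Analyses section then lists, among the feasibility outcomes, "proportion of valid wear days and weeks, and completeness of each wearable stream".

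Table 3 under Sensor Modalities describes the physical activity stream as "Step count, active minutes, and self-reported activity" and attributes it to the accelerometer, actigraphy and events entered by the participant. Heart rate comes from the wrist heart rate monitor, and the stress score is derived from heart rate variability (HRV). Under Wearable Tracker we read: "The device has a battery charge of 7 days".

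The Introduction states the primary question as the change in GHQ-12 from baseline to day 84 "associated with the change in physical activity over the 3-month study period".

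**The concern.** The rule measures data, and the outcome is labelled wear. For heart rate, HRV and stress the two should nearly coincide, because those signals need contact with the wrist. For steps and active minutes they need not. A motion sensor lying still registers no movement, and a zero from an unworn watch looks the same as a zero from a sedentary wearer. If those zeros are exported as data, the 6-hour rule accepts the day.

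Two results would suffer. The first is the wear figure, a main feasibility result meant to inform a larger study, which would be too high for the activity streams. The second is the activity exposure in the primary association. Days classed as valid enter the means, variability measures and trends as recorded, so non-wear that increases during follow-up would appear as declining activity.

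**Working it through.** The plan gives no figure for this point, so there is none to reproduce. The check is direct arithmetic on the stated rule.

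**Inputs from the protocol**
- Valid day: at least 6 hours of data (Missing Data).
- Valid week: at least 4 valid days (Missing Data).
- Follow-up: 84 days, so 84 / 7 = 12 weeks.
- Battery: up to 7 days on a charge (Wearable Tracker). One spell of non-wear on a charged watch can therefore outlast the 4-day requirement for a valid week.

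**Assumptions, not in the protocol**
- Off-wrist time is exported as zero steps.
- The step stream is judged on its own.
- True activity on worn days is constant.
- Between 0 and 3 days per week are unworn.

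**Step 1: level within a week.** With k unworn days out of 7 logged as zeros and accepted as valid, the observed weekly mean is (7 − k)/7 of the true worn-day mean.

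| Unworn days k | Observed mean / true mean | Valid days, rule as written | Valid days, wear required |
|---|---|---|---|
| 0 | 1.000 | 7/7 | 7/7 |
| 1 | 6/7 = 0.857 | 7/7 | 6/7 |
| 2 | 5/7 = 0.714 | 7/7 | 5/7 |
| 3 | 4/7 = 0.571 | 7/7 | 4/7 |
| 4 | 3/7 = 0.429 | 7/7 | 3/7, week missing |
| 7 | 0/7 = 0.000 | 7/7 | 0/7, week missing |

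With a wear criterion, the mean for k = 1 to 3 returns to 1.00 of the true value. Weeks with 4 or more unworn days drop out instead of entering as low activity.

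**Step 2: change from week 1 to week 12.** The apparent change is [(7 − k at week 12) / (7 − k at week 1)] − 1.

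- 0 to 1 day per week: 6/7 − 1 = −14.3%
- 0 to 2 days: 5/7 − 1 = −28.6%
- 0 to 3 days: 4/7 − 1 = −42.9%
- 1 to 3 days: 4/6 − 1 = −33.3%
- 1 day throughout: 6/6 − 1 = 0%

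A false decline therefore needs rising non-wear. Constant non-wear lowers the level (0.857 of true at one day per week) and leaves the change untouched.

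**Step 3: which reading of the rule applies.** The day rule can mean that each stream is judged on its own 6 hours, or that every stream must reach 6 hours before the day counts. Two places favour the first. The feasibility outcomes include completeness by stream, and Table 2 lists HRV as a morning and evening measure, which could hardly supply 6 hours daily under a joint rule.

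**The case against.** The strongest objection is that the decisive premise is missing from the protocol. Nothing says how the watch, or the export to the research platform, represents off-wrist time. If it leaves gaps, an unworn day fails the 6-hour rule and there is no bias. This stands, and it is why the point is conditional.

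Second, the day rule may be joint. An unworn day would then normally fail on heart rate. Listing valid wear days separately from stream completeness gives this some support, since the two would largely overlap if validity were per stream. I find the per-stream reading more plausible for the reasons in Step 3, but the sentence is ambiguous and needs settling either way.

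Third, the Data Collection section promises automated quality control checks, and a fuller protocol or analysis plan may handle non-wear. That is possible, but the content of the checks is not stated. The objection here is to a definition the article does fix and then labels as wear, not to a missing detail.

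Fourth, all analyses are declared exploratory. That limits the consequences for inference. It does not protect the wear figure, which is itself a feasibility result.

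A reader might go further and infer that the rule will create a spurious link between falling activity and worsening GHQ-12, because people who feel worse may wear the watch less. The protocol does not support that as a finding. It gives no non-wear rate and no relation between wear and symptoms, and if the two are unrelated no such link arises. Nor does it specify a hypothesis test whose false-positive rate could be calculated; the regressions are there to estimate effect sizes.

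**Conclusion.** The point holds in conditional form. As written, validity rests on hours of data, the outcome is called wear, and no wear criterion connects them. If streams are judged separately and off-wrist time is logged as zeros, each unworn charged day lowers the weekly activity mean by one seventh and still counts as a valid wear day. The apparent decline over follow-up is 14% to 43% if non-wear rises from none to 1–3 days per week, and nil if non-wear is constant. The non-wear range is illustrative.

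It would be wrong to conclude that an unworn watch necessarily yields valid zero-step days, or that activity will necessarily appear to fall. The first depends on the export and the second on rising non-wear, and the protocol establishes neither. The definition should still be amended, because it governs both a feasibility outcome and the exposure in the primary association, and the stream needed to repair it is already collected.

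**What to change.** In the Missing Data section:

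1. State that validity is judged per stream, which removes the ambiguity.
2. Count step and active-minute data only in hours that also contain heart-rate data from the same watch. Treat all other hours as missing, not as zero.
3. Apply the hour threshold for these streams to worn hours.
4. Express activity per worn hour, or adjust for worn hours. Otherwise a day with 6 worn hours is compared with one of 24, and shrinking partial wear could still look like falling activity.

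In the Descriptive and Feasibility Analyses section, use the same worn-hour definition for valid wear days and weeks.

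The cost is a few sentences and a merge of two streams already collected. There will be fewer valid activity days, some weeks will become missing, and the reported wear figure will be slightly less favourable.

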#### Exploratory Modelling

The primary exploratory outcome is the change in GHQ-12 score from T0 to T3. Secondary outcomes include change in other questionnaire scores. Initial associations between wearable features and mental health outcomes will be examined using simple regression models to estimate effect sizes.

#### ML Analysis

Candidate models will include a range of classifiers such as decision trees, random forests, support vector machines, and Bayesian classifiers. To reduce information leakage arising from repeated measures, models will be evaluated using participant-level grouped k-fold cross-validation, such that all observations from a given participant are assigned to either the training or test set within each fold, but not both. Hyperparameter tuning will be conducted within the training data only. Performance metrics will include area under the curve, sensitivity, and specificity for binary outcomes. ML analysis will be judged informative if (1) models can be fitted without substantial overfitting, (2) performance exceeds simple baseline models, and (3) a small number of wearable features consistently appear influential across models. Feature importance will be used to identify suitable data streams for a future larger study.

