**Methods:**

This is an observational feasibility study measuring mental health via validated questionnaires completed at baseline (T0), day 28 (T1), day 56 (T2), and day 84 (T3), and physiological metrics measured continuously via wrist-worn fitness trackers (Garmin vívosmart-5 watches) over 3 months (84 days). UK veterans will be recruited through convenience sampling methods. Statistical analysis will be exploratory, and machine learning models will be trained to detect changes in mental health and well-being outcomes.

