### Eligibility Criteria

Participants will be veterans of the UK Armed Forces who meet caseness for CMDs, including symptoms of anxiety and depression, defined by a cutoff score of ≥12 on the GHQ-12. A brief online survey will screen for study inclusion criteria and obtain informed consent from participants (Textbox 1). Eligible participants will receive a phone call from a member of the research team to confirm their delivery address for the Garmin watch, their status as a veteran via their service number, and their service history (when they served and when they left service).

Participant eligibility criteria.

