### Study Design

An observational feasibility study in which 50 UK veterans who self-report experiencing CMDs, including symptoms of anxiety and depression, will be recruited through convenience sampling methods. The target population for this study is not clinical, and there are no comparators. Participants will wear a Garmin watch, delivered to their home address, for 84 days, and complete baseline measures plus 3 monthly questionnaires about their mental health and well-being, administered on Qualtrics survey software (Qualtrics Labs, Inc). Participants will wear the devices in their everyday environment and will be sent automated email reminders to complete the monthly surveys.

Participant self-reported mental health and well-being data will be collected via monthly online questionnaires (a summary of the measures used is detailed in Table 1), and behavioral and physiological indices will be measured and collected using Garmin watches (vívosmart-5 model; Figure 2). Data will be collected via the watches on the following outcomes continuously (24/7): activity level (number of steps, active minutes, and self-reported activity), HRV, overall body battery, sleep (sleep quality, sleep score, and hours of sleep), and stress.

**Table 1 table1:** Mental health and well-being measures.

Mental health and well-being measures	Description of measure	Cutoff
Alcohol Use Disorders Identification Test for Consumption [22]	3-item measure of heavy drinking and/or active alcohol dependence. Assesses frequency and quantity of alcohol consumption, and frequency of high-intensity drinking episodes (≥6 units for women, ≥8 for men).	Scores range from 0 to 12. ≥5 indicates a positive screen. Categories: low risk (0-4), increasing risk (5-7), higher risk (8-10), and possible dependence (11-12).
12-item General Health Questionnaire [21]	Measure of common mental disorders, focusing on non-psychotic symptoms such as depression and anxiety.	Scores range from 0 to 36 (Likert scale). Caseness is defined as ≥12.
Generalized Anxiety Disorder-7 [23]	Screens for and assesses the severity of generalized anxiety disorder.	Scores range from 0 to 21. Categories: minimal (0-4), mild (5-9), moderate (10-14), and severe (15-21).
Patient Health Questionnaire-2 [24]	Brief screening tool for depression assessing frequency of low mood and anhedonia over the past 2 weeks.	Scores range from 0 to 6. ≥3 indicates probable depression.

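### The machine-learning section names only classifiers and binary-outcome metrics, although the outcomes are score changes, so it needs a dichotomisation that the article does not define and that loses information.

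*Protocol article*

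**What the plan says.** **Outcomes.** Under Exploratory Modelling the article states: "The primary exploratory outcome is the change in GHQ-12 score from T0 to T3". It continues: "Secondary outcomes include change in other questionnaire scores". The aims at the end of the Introduction give the same primary outcome and relate it to change in physical activity. Table 1 (Study Design) describes the GHQ-12 as follows: "Scores range from 0 to 36 (Likert scale). Caseness is defined as ≥12".

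**Purpose of the ML.** The Methods paragraph of the Abstract says that "machine learning models will be trained to detect changes in mental health and well-being outcomes".

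**ML methods.** ML Analysis states: "Candidate models will include a range of classifiers such as decision trees, random forests, support vector machines, and Bayesian classifiers". The metrics are then given: "Performance metrics will include area under the curve, sensitivity, and specificity for binary outcomes". The same section calls the ML informative if there is no substantial overfitting, if it beats simple baseline models, and if a few wearable features are consistently influential. Feature importance is then to pick data streams for a larger study.

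**Entry.** Eligibility Criteria requires caseness, "defined by a cutoff score of ≥12 on the GHQ-12", applied in the online screening survey.

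**Other analysis.** Exploratory Modelling also plans simple regression of mental health outcomes on wearable features.

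**Numbers.** Results reports 52 recruited, 4 withdrawn and 48 completed.

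**The concern.** The outcomes are differences between scores on ordered scales, and the ML is meant to detect change in them. The learners and metrics named need a class label. No section defines one, and no section says how large a change would count.

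Two things are at stake. First, any split of a score change discards information, and a study with about 48 completers has little to spare. Second, the ML results have a practical use: they decide whether the approach is judged informative and which sensor streams go forward. Importance rankings from a coarse or badly chosen label could favour the wrong streams.

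**Working it through.** **1. What can be reproduced.** The article states that no power calculation was done, and it gives no SD, effect size or class split. The one figure to check is the number of completers: 52 − 4 = 48, which agrees.

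**2. Outcome against method.**

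| Element | Outcome sections | ML Analysis |
|---|---|---|
| Target | Change in score | Class label, not defined |
| Learners | Simple regression | Classifiers only |
| Measure | Effect size | AUC, sensitivity, specificity |

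No regression learner and no continuous-outcome error measure is named for the ML. Applying that section to the primary or secondary outcomes therefore requires a split.

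**3. Illustrative cost of a split.** Assume a normal outcome, one value per person and a linear association. If a share p falls in one class, the share of information kept is φ(z_p)² / [p(1 − p)], where φ is the standard normal density and z_p the normal quantile of p. The splits are assumptions.

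| Split | φ(z_p) | Kept | 48 people count as |
|---|---|---|---|
| 50/50 | 0.399 | 0.637 | 30.6 |
| 30/70 | 0.348 | 0.576 | 27.6 |
| 20/80 | 0.280 | 0.490 | 23.5 |
| 10/90 | 0.175 | 0.342 | 16.4 |

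For the first row: 0.3989² / 0.25 = 0.637, and 48 × 0.637 = 30.6. The smallest possible loss under these assumptions is thus about 36%.

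**4. Precision of the named metric.** Assume a true AUC of 0.70 with one row per person, and use the Hanley-McNeil standard error. The approximate 95% interval is 0.55 to 0.85 with classes of 24 and 24 (SE 0.076), 0.53 to 0.87 with 14 and 34 (SE 0.088), and 0.50 to 0.90 with 10 and 38 (SE 0.101).

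**5. If caseness at 12 were the label.** The article does not say that it is. Under that label a move from 12 to 11 changes class, while a fall from 30 to 21 does not. To see how far the starting score alone would separate the classes, I simulated pairs of scores (400,000 per setting), all inputs being assumptions: bivariate normal, SD 6, mean 16, 18 or 20 before selection, correlation 0.4 to 0.7 between start and T3, start restricted to 12 or more, and no average change in the unselected population. The starting score alone then gave an AUC of about 0.64 to 0.83 without any wearable data, and about 3 to 9 of 48 people fell below 12 at T3. A real average improvement would raise that count.

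**The case against.** **The continuous analysis is already there.** Exploratory Modelling plans simple regression for the same outcomes, so the primary outcome is not lost. This stands, and it confines the point to the ML component. It does not remove the point, because that regression does not supply the cross-validated performance and feature importance on which the choice of streams rests.

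**The label is not stated to be caseness at 12.** A reader might infer that it must be, since this cutoff is also the entry criterion, and conclude that ML performance would mainly reflect who started just above 12. The documents do not support that:
- No section names the ML label, and a change-based label would fit the text equally well.
- Other scales have cutoffs unrelated to entry, such as PHQ-2 at 3 and the PTSD checklist at 31.
- Adverse Events contains another GHQ-12 threshold, a rise of 15 points or more between consecutive surveys, although it serves safeguarding.
- Entry is judged at screening, while the T0 GHQ-12 comes in the later baseline questionnaire, so T0 scores can lie below 12.

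Step 5 is therefore a warning about one possible choice, not a description of the plan.

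**The percentages do not describe the planned models.** This also stands. The formula assumes a linear analysis with one value per person, whereas ML Analysis describes repeated observations per participant and non-linear learners.

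**The lists are open, and details belong in an analysis plan.** The wording of both lists allows additions, and trees, forests and support-vector machines have regression forms. Further detail may also sit in a document not shown. But the article itself fixed the class of model and the type of metric, and fixed both in a form that does not fit its own outcomes.

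**Everything is exploratory.** True. This is a question of efficiency and alignment, not an error in a confirmatory test.

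**Conclusion.** The point holds for the ML component. As written, the classifiers and metrics can reach the primary and secondary outcomes only through a dichotomisation that the article does not define. That step discards information: illustratively at least 36%, and about half at a 20/80 split, for a normal outcome in a linear analysis with one value per person. The direction of the loss is secure. Its size for the planned models is not, because the article gives no SD or class split.

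It would be too strong to say that the study lacks a continuous analysis of GHQ-12 change, or that the ML cannot answer its question. Caseness at 12 would be a poor label, since it overlaps with the screening criterion and depends heavily on starting score, but nothing shows that it is the intended one. This is a worthwhile, low-cost improvement to an exploratory analysis and does not undermine the study.

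**What to change.** In ML Analysis:

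1. Add regression forms of the same learners (for example regression trees, random-forest regression and support-vector regression) for GHQ-12 change, or for T3 GHQ-12 with T0 GHQ-12 as a predictor. Name one of the two in advance, because R-squared is not comparable between them.
2. Keep the participant-grouped cross-validation and the tuning within training data as planned.
3. Report out-of-fold mean absolute error and R-squared against a model containing T0 GHQ-12 only, and name that model as one of the simple baseline comparators.
4. Base the feature importance used to choose data streams on these models.
5. Keep classification as secondary, for one pre-named change-based binary outcome that is not the entry cutoff, and report the class sizes with it.

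The cost is a few sentences and a little more analysis work, with no new data. AUC, sensitivity and specificity become secondary figures.
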